## Discussion

Ischemic-reperfusion injury has emerged as a key factor in the pathogenesis of various neurodegenerative diseases, including AD (30). This paradoxical phenomenon occurs when the restoration of blood flow to previously ischemic tissue induces cellular damage oxidative stress, and neuroinflammation, thereby exacerbating neurodegenerative processes (31). In AD, reperfusion injury is increasingly recognized as an important mechanism contributing to cognitive decline and neuronal degeneration. Recent studies have emphasized this connection. Pluta et al. highlighted the significant role of post-ischemic tau pathology in AD-related neurodegeneration, suggesting reperfusion injury may be a critical driver of disease progression (32). Ułamek-Kozioł and colleagues further supported this link by demonstrating significant proteomic and genomic alterations involving tau protein following ischemia–reperfusion events (33). Given the protective mechanisms observed with postconditioning strategies, such as reduced apoptosis, attenuated inflammatory response, and enhanced microcirculation, RIC presents a promising non-pharmacological with potential relevance to AD (34, 35). Building on these findings, the present study explores the neuroprotective efficacy of RIC in mitigating ischemia-associated cognitive decline and neurodegeneration in patients with mild Alzheimer’s dementia.

This study investigates the potential of RIC as a non-invasive, multi-target intervention for mitigating cognitive decline in mild Alzheimer’s dementia. The parameters selected for evaluation, including neuropsychological scales, plasma biomarkers, and inflammatory cytokines, provide a comprehensive framework for assessing the safety and efficacy of RIC in addressing the complex pathology of AD.

The assessment of cognitive function and daily living abilities using scales such as the MMSE, MoCA, and CDR reflects the study’s primary clinical outcomes of interest (36). These tools are widely recognized for their sensitivity and specificity in detecting changes in cognitive performance and functional status in mild Alzheimer’s dementia (8, 37), making them reliable measures for evaluating therapeutic impact of RIC. Similarly, biomarkers like Aβ40 and Aβ42, p-tau181, p-tau217, and NfL will be used to monitor disease progression and neurodegeneration (38–41). These markers are central to the pathological cascade in AD, providing insights into the molecular mechanisms modulated by RIC. Longitudinal measurement of these biomarkers enables a detailed analysis of RIC’s capacity to influence amyloid metabolism, tau pathology, and neuronal integrity (5, 42).

In addition, inflammatory cytokines, including IL-6, TNF-*α*, and CRP, will be measured to assess RIC’s effect on neuroinflammation (20, 22, 43–46). Given that neuroinflammation is a key driver of AD pathology, modulating these pathways represents a plausible mechanism through which RIC may exert its neuroprotective effects (36, 38). The inclusion of these markers facilitates a more comprehensive understanding of both systemic and central inflammatory responses to RIC.

The reliability of these parameters in supporting the study’s hypothesis is reinforced by their established roles in AD research and their responsiveness to therapeutic interventions. Neuropsychological scales are routinely employed in clinical trials to detect clinically meaningful changes in cognition and function (36). Likewise, biomarkers like Aβ and tau are well-characterized indicators of AD pathology, with fluctuations in their levels correlating with disease progression (22, 36, 38, 47, 48). Inflammatory cytokines, extensively studied as markers of immune system activity, provide insight into the inflammatory environment associated with AD (22, 48).

Furthermore, the multi-timepoint design of the study—evaluating outcomes at baseline, 3 months, 6 months, and 12 months—enhances the robustness of the findings. This approach allows for the assessment of both immediate and sustained effects of RIC, ensuring that observed changes result from the intervention rather than transient or external factors.

## Implications of findings

By integrating cognitive, functional, and biomarker assessments, this study establishes a rigorous framework for evaluating the therapeutic potential of RIC in mild Alzheimer’s dementia. The consistent use of validated scales and biomarkers ensures that the findings are both clinically relevant and scientifically credible. If successful, this research could provide a foundation for future studies exploring the broader applicability of RIC in neurodegenerative conditions.

This study has several limitations. First, the RIC treatment protocol used is pragmatic and tailored to individuals with mild dementia due to Alzheimer’s. Second, the study population is limited to patients in the mild stage of Alzheimer’s dementia meeting NIA-AA diagnostic criteria, which may introduce selection bias by excluding moderate-to-severe cases. This cohort restriction could underestimate both therapeutic efficacy (e.g., disease-modifying effects) and adverse events (e.g., cerebrovascular complications), potentially affecting the risk–benefit assessment in broader AD populations. Third, the absence of longitudinal data limits generalizability to disease progression patterns observed in advanced stages. Despite these limitations, our findings are consistent with emerging evidence supporting the neuroinflammatory modulation potential of RIC, emphasizing the need for multicenter trials with extended follow-up to validate and expand upon these preliminary results.

## Conclusion

This study’s design is integral not only to assessing RIC’s safety and efficacy but also establishes reliable indicators of its potential to modulate key pathophysiological mechanisms underlying AD progression. The strategic selection of outcome measures underscores the study’s scientific rigor and its capacity to support the hypothesis that RIC can mitigate cognitive decline in mild Alzheimer’s dementia.

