To evaluate the long-term efficacy of RIC, the study includes a 12-month follow-up period with assessments at 6 and 12 months. These evaluations include neurocognitive scales and blood biomarkers analyses. The RIC intervention itself is administered over a 3-month period, with data collection points at baseline, 3 months, 6 months, and 12 months to systematically assess its sustained effects (Figure 2).

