### Sample size estimation

This is a Phase I trial measuring the safety and feasibility of RIC. Since no prior clinical studies have examined RIC in AD patients, there is no reference data available. Ganesh proposed that a cohort of 12 patients per group is sufficient to assess the safety of remote ischemic conditioning in patients with Vascular Cognitive Impairment (28). Tong’s Phase I clinical trial on the safety and efficacy of RIC in stroke patients suggested that 20 cases are sufficient to assess the feasibility of a pilot study (29). Based on studies addressing the safety and feasibility of RIC, this project targets 20 patients in each group, providing sufficient confidence to proceed to a subsequent Phase II study with a randomized sham control.

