### Statistical analysis

Data will be obtained from all patients who complete the study protocols and follow-ups and will be analyzed using the per-protocol (PP) approach. Statistical analysis will be performed using SPSS version 20 (SPSS Inc., Chicago, IL, United States), with a significance level of *p* < 0.05. Demographics and clinical characteristics will be analyzed using descriptive statistics. Continuous and categorical data will be reported as mean values, standard deviations, number values, and percentages. Continuous variables following a normal distribution will be compared using the independent samples *t*-test, ANOVA, or rank-sum test, while categorical variables will be compared using the chi-square test.

In our RIC trial in mild Alzheimer’s dementia (*n* = 40), we implemented two strategies appropriate for small-sample longitudinal data. First, single random forest imputation was applied to address missing cognitive scores (e.g., MoCA/MMSE) by using predictors such as baseline Aβ42/Aβ40 ratio and RIC adherence preserve variable interaction structure. Second, Generalized Estimating Equations (GEE) will be used to model outcome trajectories under the assumption of missing at random (MAR), thereby accommodating incomplete data without imputation. Attrition is minimal (7% MoCA loss at 12 months) and APOE subgroup analyses show no evidence of differential dropout. This approach balances methodological rigor with feasibility and aligns with CONSORT recommendations for early-phase trials with limited resources.

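### Efficacy is tested at an unqualified p < 0.05, and the Conclusion claims support for the efficacy hypothesis, on 20 per arm chosen for safety and feasibility

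*Protocol article*

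**What the plan says.** - **Sample size estimation.** The section opens with "This is a Phase I trial measuring the safety and feasibility of RIC" and continues "Since no prior clinical studies have examined RIC in AD patients, there is no reference data available". The number comes from two earlier RIC studies (12 per group for safety, 20 cases for feasibility). The section ends: "this project targets 20 patients in each group, providing sufficient confidence to proceed to a subsequent Phase II study". No effect size, SD or power is given.
- **Abstract and Outcomes for efficacy.** The Abstract makes the four clinical scales (MMSE, MoCA, CDR, ADL) primary for efficacy. Outcomes for efficacy lists the same scales as secondary.
- **Statistical analysis.** Tests are run "with a significance level of *p* < 0.05", by t-test, ANOVA, rank-sum or chi-square, and outcome trajectories are modelled by GEE. On data summaries: "Continuous and categorical data will be reported as mean values, standard deviations, number values, and percentages". Efficacy tests are not marked as exploratory.
- **Interventions.** "The RIC intervention itself is administered over a 3-month period", with assessments at baseline, 3, 6 and 12 months.
- **Discussion and Conclusion.** The Discussion says the multi-timepoint design ensures that observed changes are due to the intervention. The Conclusion says the choice of outcome measures underscores the study's rigor and "its capacity to support the hypothesis that RIC can mitigate cognitive decline".
- **Implications of findings.** The limitations listed do not include the small sample.

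**The concern.** The sample was chosen for one purpose, and the threshold and the conclusion serve another. A sample set by precedent for safety and feasibility may be entirely adequate for that. It does not follow that it can support or refute a hypothesis about slowing cognitive decline, and the article contains no figure that would show it can.

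The trial is meant as a foundation for later work and as the basis for going on to Phase II. If efficacy is read through p < 0.05, there are two ways to be misled. An uninformative null could be taken as a sign that RIC does not work. Or a significant result, which at this size can arise only from a large observed difference, could be taken at face value and carried into the planning of the next trial.

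**Working it through.** **There is no efficacy figure to reproduce.** The 20 per arm rests on precedent alone. What can be computed is what 20 per arm delivers.

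**Inputs from the article:** n = 20 per arm, 1:1, alpha 0.05, two-group comparison of a continuous outcome. Two-sided testing is assumed, because sidedness is not stated.

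**1. Precision, in SD units (no clinical assumption).**
Half-width = t(0.975, 38 df) × √(2/20) = 2.024 × 0.316 = 0.64 SD. By the same algebra, an observed difference must exceed about 0.64 observed SD to be significant.

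**2. Power, in SD units (no clinical assumption).**
Exact power from the noncentral t with 38 df and noncentrality d × √(20/2) = 3.162 × d:

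| True difference d (SD) | Power |
|---|---|
| 0.2 | 9.5% |
| 0.3 | 15% |
| 0.5 | 34% |
| 0.8 | 69% |
| 0.91 | 80% |
| 1.0 | 87% |

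The planned per-protocol analysis of completers can only lower n. At 18 per arm, 80% power needs 0.96 SD.

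**3. Overstatement when significant.**
Simulated two-sample t-tests, normal data, 20 per arm. The table gives the mean absolute size of the significant estimates divided by the true difference:

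| True d | Ratio |
|---|---|
| 0.3 | 2.6 |
| 0.5 | 1.67 |
| 0.75 | 1.24 |
| 1.0 | 1.08 |

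**4. In MMSE points (assumptions; the article gives neither decline rates nor SDs).**
Assume linear untreated decline of 2-3 points a year and an SD of 3-month change of 2-3 points. Full arrest over the 3-month course is then a difference of 2/4 = 0.50 to 3/4 = 0.75 points.
- Least favourable: d = 0.50/3 = 0.167, power 8%.
- Most favourable: d = 0.75/2 = 0.375, power 21%.
- Interval half-width: 0.64 × 2 = 1.3 to 0.64 × 3 = 1.9 points, wider than the whole effect.

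Sensitivity to these assumptions:
- 1 point a year with SD 3.5: power 5.6%.
- 4 points a year with SD 2: 34%. With SD 1.5: 54%.
- Arrest lasting all 12 months (2-3 points, SD of 12-month change 3-4): d = 2/4 = 0.5 to 3/3 = 1.0, power 34-87%.

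**The case against.** The strongest reply is that the article does not hide any of this. It calls itself Phase I, describes efficacy as preliminary, speaks of potential effectiveness, and asks for multicenter trials to follow. The sentence in the Conclusion ties the capacity to the choice of outcome measures, not to the sample size, and as closing prose it governs no analysis. This stands in part: low efficacy power is not itself an error here. But well-chosen scales cannot supply the precision that 40 patients lack, and an analysis plan could not correct the article's own Discussion and Conclusion.

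Four stronger readings are tempting, and the document does not support them.

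- **That only means and SDs will be reported.** The sentence on data summaries follows one about demographics and clinical characteristics. The same section plans group tests and a GEE, which yields estimates and standard errors. Interval reporting may also sit in a full protocol or analysis plan that is not shown, so silence on intervals is not the defect.
- **That full arrest of decline would almost always be missed.** This depends on decline rates and SDs that the article does not give. It is a fair description of arrest confined to the 3-month course under the assumptions above. It fails with faster decline and a smaller SD, and for arrest lasting 12 months, which the planned follow-up is meant to examine.
- **That any significant result must be a large overestimate.** At a true 1.0 SD the overstatement is only about 8%.
- **That a null will be read as no effect, or that Phase II will be sized from the observed effect.** The article says neither. These are risks that its wording leaves open, not stated rules.

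The GEE may gain some precision over a single-visit comparison. It is unlikely to change the picture for a 3-month effect of 0.2-0.3 SD.

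**Conclusion.** The point holds as a mismatch between the basis for the sample size and the way efficacy is tested and described. Without any clinical assumption, 20 per arm gives a 95% interval of about ±0.64 SD and reaches 80% power only near 0.91 SD. Non-significance is therefore uninformative for modest effects, and significance overstates them, by an amount that shrinks as the true effect grows.

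The MMSE illustration (8-21% power for full arrest during treatment) is conditional on the assumed decline and SD and should always be quoted with them. The SD-unit results rest on two-sided testing, approximate normality and 20 analysed per arm.

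This is worth changing because it alters what the trial may conclude about efficacy. It casts no doubt on the sample size for safety and feasibility.

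**What to change.** - **Statistical analysis:** state that all efficacy analyses are exploratory. Report each efficacy outcome as a RIC-minus-sham difference with a 95% confidence interval, from the planned GEE or the two-group comparison. State that efficacy is neither claimed nor rejected on p < 0.05.
- **Conclusion:** replace the claim of capacity to support the hypothesis with the aim of estimating the between-group difference and its variability for planning Phase II, and give the expected half-width (about 0.64 SD).
- **Discussion:** soften the statement that the design ensures changes result from the intervention.
- **Implications of findings:** add small sample size to the limitations.
- **Abstract and Outcomes for efficacy:** give the four clinical scales the same status in both places.

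The cost is wording and a more modest efficacy claim. No extra patients, visits or data are needed.

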## Glossary

RIC: Remote Ischemic Conditioning
AD: Alzheimer’s disease
HAMA: Hamilton Anxiety Rating Scale
HAMD-17: Hamilton Depression Rating Scale
MMSE: Mini-Mental State Examination
MoCA: Montreal Cognitive Assessment
CDR: Clinical Dementia Rating
ADL: Activities of Daily Living
Aβ: β-amyloid
VCI: Vascular cognitive impairment
DSMB: Data and Safety Monitoring Board
NIA-AA: National Institute on Aging and Alzheimer’s Association
ELISA: Enzyme-linked immunosorbent assay
IL-1β: Interleukin-1β
IL-6: Interleukin-6
IL-8: Interleukin-8
IL-10: Interleukin-10
IL-2R: Interleukin-2 receptor
TNF-α: Tumor necrosis factor-α
ESR: Erythrocyte sedimentation rate
CRP: C-reactive protein
GFAP: Glial fibrillary acidic protein
NfL: Neurofilament light chain
PP: Per-protocol
MAR: Missing at random
